### Measures

Data will include quantitative surveys, qualitative interviews, and independent evaluator assessments over two years for each cohort (see Table 1).

**Table 1 Tab1:** Study measures

			**Spring YR 0**	**Year 1**			**Year 2**	
	**Focus**	**Data source**	**Implementation** **screen/baseline**	**RUBIES screen/baseline**	**Week 16**	**Week** **24**	**Week 52**	**Week** **76**
**School**								
Characteristics	Characterization	Record review	X					
RUBIES School Implementation Leadership Scale*	HELM Mediator	HELM Educator	X		X	X	X	X
RUBIES School Implementation Climate Scale*	HELM Mediator	HELM Educator	X		X	X	X	X
**Student**								
Autism Classification	Characterization	Record review		X				
Demographics	Characterization	Parent		X				
School Services	Characterization	Educator		X	X	X		
SRS-2	Characterization	Educator		X				
SESBI-R	Primary Effective	Educator		X	X	X		
EDI	Secondary Effective	Educator		X	X	X		
CGI-Improve (Child Externalizing Behavior)	Secondary Effective	Educator + IE			X	X		
ABC-I	Secondary Effective	Educator		X	X	X		
CGI-Student Self-Management	RUBIES Mediator	IE			X	X		
**Educator**								
Demographics	Characterization	Educator	X					
RUBIES Educator BSP Implementation*	Primary Implement	Educator + IE			X	X	X	X
CGI-Sustain (Educator Sustainment of RUBIES Strategies)*	Secondary Implement	Educator + IE			X	X	X	X

^*^RUBIES and RUBIES + HELM Condition only

#### Demographics and context

School personnel will complete a demographic form in the Spring (Year 0). At clinical baseline of Year 1, Week 16, and Week 24, educators will document percent time and activities where the student is included in general education settings. School characteristics (e.g., school size, percent eligible for free lunch, racial/ethnic composition) will be obtained via school records in Spring of Year 0. Caregivers will complete a demographic form on students at baseline of Year 1.

 Autism Classification will be based on a documented autism diagnosis via school records (i.e., Individualized Education Program) collected at baseline of Year 1. Additionally, at baseline Year 1, educators will complete the Social Responsiveness Scale-2 (SRS-2,) a 65-item rating scale that measures social behavior associated with autism [47]. The SRS-2 has been used to distinguish autistic children from those with other psychiatric conditions.^107^The SRS-2 is used for children between the ages of 4–18 years with internal consistency of 0.88, inter-rater reliability of 0.75, and test–retest reliability of 0.88 [47].

#### Clinical outcomes

Student externalizing behavior will be rated at clinical baseline, Weeks 16, and 24. The Sutter Eyberg Student Behavior Inventory-Revised (SESBI-R; primary clinical effectiveness outcome) [43] is an educator-reported measure used to assess conduct problems in youth ages 2–16. It contains 38 items on which teachers indicate the current frequency of behavior problems (Never to Always) and indicate whether or not they find the behaviors problematic. The Intensity and Problem scales of the SESBI-R have demonstrated internal consistency coefficients of 0.98 and 0.96 and test–retest correlations of 0.87 and 0.93, respectively [48].

The Emotion Dysregulation Inventory [44] (EDI, secondary clinical effectiveness outcome) is a questionnaire that assesses emotion regulation and is validated for autistic youth. Educators rate the youth’s observed functioning over the past 7 days using a 5-point Likert scale from “not at all” to “very severe.” The EDI has excellent internal consistency (Cronbach’s alpha > 0.90) [49].

The Aberrant Behavior Checklist [50, 51] (ABC)-Irritability Subscale (secondary clinical effectiveness outcome) measures behavioral challenges in individuals with developmental disabilities. Educators rate items on a scale of 0 “never a problem” to 3 “severe problem.” Higher scores indicate greater problems. This study will utilize the Irritability subscale as it has been used in previous RUBI trials and is sensitive to change with intervention [16, 21]. The irritability subscale has excellent internal consistency (Cronbach’s alpha > 0.90) [52].

The Clinical Global Impressions-Improvement Scale [53] (CGI-I, secondary clinical effectiveness outcome), which is used widely in pharmacological and clinical trials to standardize assessment of overall change or improvement in targeted behaviors or outcomes [53, 54], is an assessment tool used to establish the improvement from baseline in defined intervention targets (e.g., focal behaviors) following treatment. The CGI-I is rated on a 7-point scale from 1 “very much improved”, to 4 “No Change” to 7 “very much worse.” Only scores of 1 and 2 will be demarked as a positive response to treatment. The CGI-I will be completed by a masked independent evaluator (IE) to assess improvement in student externalizing behaviors. CGI-I ratings are based on individualized narratives (intensity, frequency, duration) of student externalizing behavior provided by the educator via interview with the IE. The educator and IE then review and update the narrative at subsequent assessment points (Weeks 16 and 24). Using the updated narrative, along with other available information (educator ratings of behaviors on the EDI, SESBI-R and ABC-I), the IE completes the CGI-I rating. The CGI-I has been used in prior trials of RUBI and has been shown to be sensitive to detecting change in intervention-specific targets as well as differences between interventions [16, 17].

#### Implementation outcomes

Sustainment (primary implementation outcome) is defined as the level of educator fidelity to RUBIES through the second year of study enrollment (Weeks 52 and 76). Fidelity to RUBIES is operationalized on the RUBIES Educator Behavior Support Plan Implementation (BSPI) measure which will be rated by a trained independent evaluator masked to study condition. The BSPI is designed to assesses the educator’s current implementation of strategies that are detailed on the Behavior Support Plan, which is an organizing document that captures all RUBIES strategies developed for the educator’s student in collaboration with the RUBIES coach and implemented by the educator in Year 1. The IE rating on the BSPI will be completed at Weeks 16, 24, 52, and 76 and will be based on discussion with the educator around their current implementation of RUBIES strategies documented on their behavior support plan. Ratings on the BSPI are based on a scale of 1–8 (1 “none of the components of the behavior support plan are being implemented”; 4 “behavior support plan is partially implemented and with some implementation errors”; 8 “the behavior support plan is implemented consistently as intended in its entirety”). In a prior study of RUBIES, BSPI scores of educators randomized to RUBIES averaged 6.78 (SD = 1.25; scale of 1–8) [21].

The IE also will rate the Clinical Global Impressions-Sustainment scale (CGI-S, secondary implementation outcome), an adapted version of the Clinical Global Impressions-Improvement scale. The CGI-S will be rated by the IE on a 7-point scale from 1 “very much improved”, to 4 “no change” to 7 “very much worse.” To inform CGI-S ratings, a standardized questionnaire followed by IE interview will be conducted with educators at implementation baseline to establish a benchmark of the educator’s baseline skills. The questionnaire allows the educator to endorse whether, at baseline, they use any of 26 specific RUBIES strategies (yes/no response). The interview between IE and educator then focuses on characterizing the quality and frequency of endorsed strategies. Finally, the IE will use all information to characterize the educator’s overall skill mastery at baseline on a 7-point scale (1 “exceptional mastery”; 4 “developing mastery”; 7 “no demonstrated mastery”), which will allow the IE to standardize subsequent CGI-S ratings across educators who have variable foundations in behavioral strategies at baseline. At Weeks 16, 24, 52, and 76, the educator will update their current strategy “use” ratings and then meet with the IE to update characterization (quality/frequency) of the utilized RUBIES strategies. Using this updated information, the IE will complete the CGI-Sustainment rating (i.e., is the current use of educator RUBIES strategies 1 “very much improved”, 2 “much improved”, 3 “minimally improved”, 4 “no change”, etc. from baseline). RUBIES sustainment at Weeks 52 and 76 will be calculated as a binary variable: strategies “sustained” over time (Score of 1 or 2 – Much improved to very much improved from baseline) vs strategies not “sustained” over time (Score of ≥ 3: No Change to Very Much Worse from baseline).

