There are currently no widely disseminated evidence-based interventions for educators to effectively and efficiently address externalizing behavior of autistic children in schools. The Research Units on Behavioral Interventions in Educational Settings (RUBIES) intervention is a promising intervention designed to help educators functionally evaluate and understand autistic children’s externalizing behavior as communication, and to account for autistic characteristics (e.g. rigidities and sensory sensitivities) in responding to that behavior [15]. RUBIES was adapted from RUBI, an empirically-validated caregiver-mediated behavioral intervention for autistic children with co-occurring externalizing behaviors [16, 17]. The adapted RUBIES intervention includes 9 modules and provides a simple framework that helps teach educators how to identify the function of a child’s behavior in order to apply a tailored positive behavioral support strategy that addresses the behavior’s function [18–20]. Previous studies indicate RUBIES is feasible, acceptable, and appropriate for schools; however, its clinical effectiveness in reducing child externalizing behaviors in schools has yet to be evaluated [21].

Clinical interventions such as RUBIES cannot meaningfully improve population health if they are not implemented with fidelity (i.e., the extent to which the intervention is implemented as designed) and sustained (i.e., the degree to which the intervention continues to be delivered with fidelity in a setting) over time [22, 23]. Malleable organization-level factors, including leadership, culture and climate, and operating policies and procedures, frequently stymie efforts to implement autism interventions with fidelity in schools and sustain them over time [24–26]. Previous research has highlighted two related malleable organizational factors that are particularly effective in predicting evidence-based practice (EBP) fidelity: implementation leadership (i.e., specific leader behaviors that support EBP use) and implementation climate (i.e., shared perceptions among intervention users of the extent to which EBP use with fidelity is expected, supported, and rewarded within the setting) [24, 27–29]. Research indicates that implementation strategies targeting implementation leadership and climate can improve fidelity to and the effectiveness of clinical interventions, as well as create an environment that is conducive to EBP sustainment over time [30–32].

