## Method

### Study design

This study will use a hybrid type 2 effectiveness-implementation trial with HELM, RUBIES, and a psychoeducation only control condition to provide a rigorous test of the effects of RUBIES and HELM across 126 educators paired with 126 autistic children in 42 elementary schools. The full sample of 42 elementary schools will be enrolled in three cohorts of approximately 14 schools each nationwide. Each cohort will participate for two years. Depending on arm, educators will complete study instruments up to six times: 1) Spring semester prior to the year of school and student enrollment (implementation baseline; arms 1–2); 2) Fall semester Year 1 (clinical baseline; arms 1–3); 3) 16 weeks (arms 1–3); 4) 24 weeks (arms 1–3); 5) 52 weeks (arms 1–2); and 6) 76 weeks (arms 1–2). Leaders and educators will be compensated $40 at implementation and clinical baseline, $50 at Week 16, $60 at Week 24, $70 at Week 52, and $80 at Week 76 for the completion of study instruments at each timepoint. See Fig. 3 for study design.

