### Aim 2 analyses

Aim 2 compares the effect of HELM vs. educator coaching on RUBIES sustainment as measured by BSPI scores (arm 1 vs. arm 2). The hypothesis states that intervening with HELM will induce better sustainment (i.e., higher RUBIES fidelity) in Year 2 at Week 52 and Week 76 compared to educator coaching only. The two observations of sustainment for each educator (paired 1:1 with a child) in Year 2 are nested within the educator, who is nested within a school. For this outcome, we will fit an LMM with the following hierarchical structure: the Level 1 model (observation) will include Week 52 and Week 76 fidelity observations for each educator. This level does not include a growth model because we do not assume fidelity will systematically increase or decrease during the sustainment school year; instead, we assume random fluctuation around an educator mean for the year. At Level 2 (educator), we will include a random intercept and educator-level covariates such as years of experience which may be a potential confounder. Covariates will be selected as described above. At Level 3 (school), we will include a random intercept and a treatment assignment indicator (RUBIES + HELM vs. RUBIES only) which will be contrast coded to facilitate main effect interpretations. The coefficient for the treatment assignment indicator in this model will test whether RUBIES sustainment (i.e., level of RUBIES fidelity in the second year of study enrollment) was superior for educators assigned to RUBIES + HELM compared to educators assigned to RUBIES only at Week 52 and Week 76. As a secondary implementation outcome, we will analyze a binary indicator of RUBIES sustainment at Week 52 and Week 76 (based on the CGI-S) to evaluate whether HELM improved the odds of sustaining RUBIES at a provisional ‘sustainment’ cutoff. This analysis will use a similar model as Aim 2, but data from different timepoints or distributions (LMM and Generalized LMM for binary outcomes).

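### The binary CGI-Sustainment outcome measures improvement since before RUBIES coaching, not sustainment, and its label for score 3 contradicts the scale

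*Protocol article*

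**What the plan says.** Under Implementation outcomes, the protocol article describes the CGI-Sustainment scale (CGI-S) as a 7-point change scale: 1 very much improved, 2 much improved, 3 minimally improved, 4 no change, 7 very much worse. A questionnaire and interview "will be conducted with educators at implementation baseline to establish a benchmark" of the educator's skills. Study design places that visit in the "Spring semester prior to the year of school and student enrollment (implementation baseline; arms 1–2"), so it precedes RUBIES coaching. At the same visit "the IE will use all information to characterize the educator’s overall skill mastery at baseline on a 7-point scale", running from 1 (exceptional) to 7 (none demonstrated).

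The scale is rated again at Weeks 16, 24, 52 and 76. At Weeks 52 and 76 it is cut in two:
- sustained: "Score of 1 or 2 – Much improved to very much improved from baseline"
- not sustained: "Score of ≥ 3: No Change to Very Much Worse from baseline"

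Aim 2 analyses then uses the binary variable in a generalized linear mixed model, arm 1 against arm 2, "to evaluate whether HELM improved the odds of sustaining RUBIES", and calls the cutoff provisional. Background defines sustainment differently, as "the degree to which the intervention continues to be delivered with fidelity in a setting". The primary implementation outcome (BSPI) is likewise a level of fidelity in Year 2.

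**The concern.** A variable called sustainment should say whether practice reached through coaching is still being delivered. This one says whether the educator is clearly better than before coaching began. The two can part company in both directions: good practice that was there from the start counts as failure, and some decline after coaching does not show.

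The CGI-Sustainment scale is the only outcome that Table 1 marks as secondary implementation, and it gives the only yes/no statement on sustainment. If the result is reported as the odds of sustaining RUBIES, readers will take it for something it does not measure. Educators who cannot pass because they began near the top also dilute the comparison of HELM with coaching alone.

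Separately, the label for the failing category starts at no change, whereas the category starts at 3, which the scale defines as minimally improved. The same label is attached to the CGI-SM under RUBIES mediator.

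**Working it through.** **1. Figure to reproduce.** There is none. Sample size and power covers Aim 2 through the BSPI only and gives no expected rate or power for the binary CGI-S.

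**2. The rule applied literally.** Room for improvement on the baseline mastery scale is (baseline rating − 1) steps: 0 for an educator rated 1, 1 for a rating of 2, 6 for a rating of 7. Taking CGI-S scores at Week 24 and Week 76:

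| Week 24 | Week 76 | Coded as |
|---|---|---|
| 1 | 1 | sustained |
| 1 | 2 | sustained (decline not seen) |
| 1 | 3 or 4 | not sustained |
| 2 | 2 | sustained |
| 2 | 3 or 4 | not sustained |
| 4 | 4 | not sustained, including an educator stable at exceptional mastery |

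**3. Effect on the odds ratio (illustration).** Assumptions not taken from the protocol: true sustained rates of 80% with HELM and 60% without, and a share f of educators in each arm who cannot reach a score of 1 or 2. Observed rate = true rate × (1 − f). OR = [p1/(1 − p1)] / [p0/(1 − p0)].
- f = 0: 0.80 and 0.60; OR = 4.00/1.50 = 2.67
- f = 5%: 0.76 and 0.57; OR = 3.167/1.326 = 2.39
- f = 15%: 0.68 and 0.51; OR = 2.125/1.041 = 2.04

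**4. Educators miscoded.** Only those who cannot qualify *and* truly sustain are wrongly coded. With the 84 educators of Aim 2 and an average true rate of (80% + 60%)/2 = 70%:
- f = 5%: 84 × 0.05 × 0.70 = 2.9
- f = 15%: 84 × 0.15 × 0.70 = 8.8

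That is about 3 to 9 educators. After the protocol's 25% attrition (× 0.75) it is about 2 to 7.

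**5. Effect on power (second illustration).** Here the assumed rates are 80% and 50% among educators with room to improve. The protocol gives 42 educators per arm, 25% attrition, three dyads per school and 10% clustering. Reading the last two as a design effect of 1 + (3 − 1) × 0.10 = 1.2 gives 42 × 0.75 / 1.2 = 26.25 effective educators per arm. A two-sided 5% comparison of two proportions, one observation per educator, gives:

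| f | Rates | Difference (points) | Power |
|---|---|---|---|
| 0% | 80% vs 50% | 30 | 63% |
| 10% | 72% vs 45% | 27 | 51% |
| 20% | 64% vs 40% | 24 | 41% |

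The planned model uses both Year 2 visits, so the absolute power figures are only indicative. The downward trend is the point.

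**The case against.** **The ceiling may be handled by the raters.** The protocol says the baseline mastery rating is one "which will allow the IE to standardize subsequent CGI-S ratings across educators who have variable foundations in behavioral strategies at baseline". The CGI-S is a global judgement over 26 strategies, not a difference between two mastery scores, and the rater manual may say how to treat a skilled starter. This softens the claim that such an educator must be rated 4. It does not remove it: the anchors remain change from baseline and the cutoff still demands improvement.

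**Few educators may start near the top.** Schools with earlier RUBIES exposure are excluded, and Background says most educators have limited training for autistic students. That points to a small share. Against it, special education teachers and school psychologists are eligible, and the text itself expects varied starting skill. The share is unknown.

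**Imbalance between arms is partly covered.** Randomization balances starting skill in expectation, and Aim 2 admits covariates whose difference across arms reaches 0.2. This stands, which is why the problem is not systematic bias between arms.

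**Improvement still present at Week 76 is a reasonable marker.** In schools new to RUBIES it does suggest retained gains. This supports keeping the variable under an accurate name.

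**A stronger reading.** A reader might infer that an educator who loses most of the gains can still be coded as sustained. The protocol does not support that. It gives no mapping from mastery steps to CGI-S scores, and such an educator would naturally be rated 3 or worse and fail. Only the slip from 1 to 2 is certain to be hidden.

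**The label slip changes no coding.** This is correct, because the numeric rule of 1–2 against 3 or more is clear. The wording still needs repair.

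**Conclusion.** The point holds for this secondary outcome. The binary CGI-S is anchored to a pre-coaching baseline and needs marked improvement, so it does not match the protocol's own definition of sustainment or the way Aim 2 interprets it. Stable high skill is coded as failure, and one step of decline from the top score is invisible. The label for scores of 3 or more contradicts the scale in the same section.

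The size depends on a share the protocol does not give. Over an assumed range of 5% to 15% unable to qualify, an odds ratio of 2.67 would be observed as 2.39 to 2.04, with about 3 to 9 of 84 educators miscoded before attrition. These figures treat all such educators as unable to pass, which is certain for none and least clear for those at mastery 2, who have one step of room. The loss is of meaning and sensitivity. The primary implementation outcome, a BSPI level, is not touched.

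**What to change.** 1. Name, analyse and report the present binary CGI-S as improvement from baseline, and stop describing it as the odds of sustaining RUBIES.
2. Put the baseline mastery rating, which is already collected, into the generalized linear mixed model as a prespecified covariate, whether or not the arms differ on it.
3. Relabel scores of 3 or more as minimally improved to very much worse, for both the CGI-S and the CGI-SM.
4. If a yes/no sustainment outcome is wanted, have the independent evaluator re-rate the same 7-point mastery scale at the interviews already held at Weeks 16, 24, 52 and 76. Define sustained before enrolment, either as a level at Weeks 52 and 76 or as maintenance of the post-coaching level at Weeks 16/24.

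The first three changes cost only wording and one model term. The fourth costs one extra single-item rating per interview and a cutoff without prior use, though the present one is already called provisional. Neither definition is free of drawbacks. A fixed level can hide decline within the passing range and also passes an educator who met it before training. A post-coaching reference is measured after HELM has begun, so it may itself differ by arm. The choice should be stated with its reason. The Discussion reports no participants enrolled as of February 2026, so on that date all four changes could still precede data collection.

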#### RUBIES mediator

We hypothesize that RUBIES will result in reduced student externalizing behavior by increasing students’ use of self-management skills that are taught by their educator (e.g., use of a functional communication tool to request help/break, independent reference to visual support, engagement with self-regulatory strategy such as fidget, movement to calming corner). For example, functional communication training involves a teacher instructing the child on how to use a more functional communication request (e.g., “I need a break”). Successful reduction of challenging behavior is thus reliant, in part, on the child’s use of self-management skills. To assess this hypothesized mediator, student self-management skills will be rated at Weeks 16 and 24 by a trained independent evaluator (IE) masked to study randomization utilizing the Clinical Global Impressions-Self Management (CGI-SM) scale, an adapted version of the Clinical Global Impressions-Improvement scale [53, 54]. The CGI-SM will be rated by the IE on a 7-point scale from 1 (very much improved), to 4 (No Change) to 7 (very much worse). To inform CGI-SM ratings, a standardized questionnaire will be completed by the educator, followed by IE interview will be conducted at baseline. The questionnaire will allow the educator to endorse whether, at baseline, their student uses any of 16 specific self-management/self-regulation skills that are emphasized in RUBIES (yes/no response). The interview between IE and educator will then focus on characterizing the quality and frequency of the student’s use of endorsed strategies. At Weeks 16 and 24, the educator will update their student’s current strategy “use” ratings and then meet with the IE to update characterization (quality/frequency) of the utilized self-management strategies. Using this updated information, the IE will complete the CGI-SM rating (i.e., is the student’s current use of RUBIES self-management strategies are very much improved (1), much improved (2), minimally improved (3), no change (4), etc. from baseline). Effectively using self-management strategies will be calculated as a binary variable based on the CGI: effectively using self-management strategies (CGI Score of 1 or 2: Much Improved or Very Much Improved from baseline) versus not effectively using self-management strategies (CGI Scores ≥ 3: No Change to Very Much Worse from baseline).

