### Aim 1 analyses

Aim 1 evaluates the main effect of RUBIES vs. educator psychoeducation on child externalizing behavior among children in Year 1 of study enrollment. The primary outcome for this comparison is change in child externalizing behavior from baseline to Week 24, contrasting all groups assigned to RUBIES vs. educator psychoeducation (i.e., arms 1 & 2 vs. arm 3). We will fit a three-level Linear Mixed Model (LMM) as follows: the Level 1 model (piece wise time) with a “knot” (i.e., inflection point) at Week 16 used to capture each child’s change in externalizing behavior from Baseline to Week 16, and potentially different slope from Week 16 to Week 24. At Level 2 (child/educator; due to 1:1 pairing), each growth parameter will be modeled as a function of an intercept and child/educator-level covariates. We will select covariates by testing for differences across arms on youth and educator characteristics; covariates will be included if the effect size ≥|0.2|. At Level 3 (school), we will include a random intercept to account for the nesting of the child-educator dyads within schools and a treatment assignment indicator ([RUBIES + HELM] + [RUBIES only] vs. educator psychoeducation). We will test the interaction effect of treatment condition with time. Linear combinations of the growth parameters from this model will be used to test whether improvement in child externalizing behavior was superior for autistic children assigned to [RUBIES + HELM] + [RUBIES only] vs. educator psychoeducation from Baseline to Week 24.

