Aim 3 involves mediation analysis to evaluate the mechanisms that link RUBIES to children’s externalizing behavior and HELM to RUBIES sustainment as measured by the BSPI. The primary focus will be testing the main effects of RUBIES on the hypothesized mediator, children’s self-management skills, and of HELM on its hypothesized mediators, implementation leadership and climate, in order to establish the discriminant effects of these exposures relative to their comparators. Following these primary analyses, exploratory analyses will be used to test the remainder of the mechanistic chain proposed by RUBIES. These analyses will use the product of coefficients approach to mediation and will build on the foundational Aim 1 model [63–66]. The same approach will be used for the HELM mediators, using the model for Aim 2 as the foundational model. Consistent with best practices, we will conduct robustness checks and sensitivity analyses regarding the sequential ignitability assumption and other assumptions of our mediation analyses following model estimation [67].

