For Aim 3, we focused the power calculation for the mediation aim on the effects of RUBIES on the hypothesized mediator, children’s self-management skills, in order to establish the discriminant effects of RUBIES relative to educator psychoeducation. Based on Heath et al., [68] children’s self-management skills have a moderately large effect for decreasing challenging behaviors (mediator on outcome). While we do not have preliminary data for the relationship between RUBIES on self-management skills, the power calculation is presented assuming small (0.25) and moderate (0.5) effects of RUBIES on self-management skills (treatment on mediator). With an effective sample size of 126 autistic children nested within 42 schools, we have 67% and 99% power to detect an indirect effect of RUBIES on children’s externalizing behavior assuming 1) small and moderate effects of RUBIES on self-management skills, respectively; 2) a moderate effect of self-management skills on decreasing externalizing behaviors; [68] 3) smaller effect of RUBIES on children’s externalizing behavior (Aim 1; treatment on outcome); and 4) Type I error rate of 0.05.

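### The 7-point self-management mediator is given only a binary scoring, but the 67% and 99% power figures for Aim 3 reproduce only for a continuous mediator

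*Protocol article*

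**What the plan says.** Under RUBIES mediator, an independent evaluator rates the CGI-SM from 1 (very much improved) through 4 (no change) to 7 (very much worse) at Weeks 16 and 24. The section then fixes the scoring: "Effectively using self-management strategies will be calculated as a binary variable based on the CGI". Scores 1 and 2 count as effective use. Scores of 3 or more do not, so minimal improvement (3) is pooled with no change and deterioration.

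The Aim 3 paragraph, printed at the end of Aim 2 analyses, makes the effect of RUBIES on this mediator the primary focus. After that, "exploratory analyses will be used to test the remainder of the mechanistic chain proposed by RUBIES". On method: "These analyses will use the product of coefficients approach to mediation and will build on the foundational Aim 1 model". The Aim 1 model is linear: "We will fit a three-level Linear Mixed Model (LMM) as follows".

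Sample size and power (Aim 3) reports 67% and 99% power for the indirect effect, "assuming small (0.25) and moderate (0.5) effects of RUBIES on self-management skills", with 126 children in 42 schools and a Type I error rate of 0.05. It gives no responder rate, risk difference or odds ratio.

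**The concern.** Path effects of 0.25 and 0.5 labelled small and moderate are standardized effects on a continuous scale. The variable defined in the measures section is a yes/no split of a 7-point rating. A split carries less information than the rating, and how much less depends on where the cut falls in the sample.

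Two things are at stake. The primary Aim 3 test, treatment on mediator, is made weaker than the collected data allow. And the power quoted for the mediation aim may not describe the variable that will be analysed, so a null mechanism result could be read as evidence against the theory when the test had little chance of success.

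**Working it through.** **Inputs from the protocol.** Path a (treatment on mediator) = 0.25 or 0.5; 126 children; alpha 0.05 (two-sided assumed); allocation 84 vs 42; school ICC 0.10 with 3 dyads per school.

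**Assumed inputs.** Path b (mediator on outcome) is only called moderate; taken as 0.5. Path c' (treatment on outcome) is only called smaller; taken as 0.14 to 0.25. Design effect = 1 + (3 − 1) × 0.10 = 1.2, so n = 126/1.2 = 105.

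**Step 1: reproduce 67% and 99%.** Product-of-coefficients (Sobel) power with a continuous standardized mediator:
- var(a) = (1 − a²)/(n − 2)
- R² = b² + c'² + 2abc'
- var(b) = (1 − R²)/[(n − 3)(1 − a²)]
- z = ab/√[a² var(b) + b² var(a)]; power = Φ(z − 1.96)

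Small path, c' = 0.25: var(a) = 0.9375/103 = 0.00910; R² = 0.375; var(b) = 0.625/(102 × 0.9375) = 0.00654; SE = 0.0518; z = 0.125/0.0518 = 2.41; power 67.5%.

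Moderate path, c' = 0.25: var(a) = 0.75/103 = 0.00728; R² = 0.4375; var(b) = 0.5625/(102 × 0.75) = 0.00735; SE = 0.0605; z = 0.25/0.0605 = 4.13; power 98.5%.

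With c' = 0.14 the results are 66.7% and 97.7%. All are within about 2 points of the stated figures.

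Other readings tried:
- n = 126, Sobel, b = 0.5: 74–75% and 99%.
- n = 126, joint significance test, b = 0.5: 82% and over 99%.
- 0.25 and 0.5 read as Cohen's d, n = 126: 25–26% and 67–75%.
- n = 101 (126 × 0.8, the Aim 1 attrition), b = 0.59, c' = 0.25: 68.5% and 99.6%. This also fits, and it too is a continuous mediator.

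**Step 2: same setting, binary mediator.** Simulation with n = 105 (70 vs 35), b = 0.5, c' = 0.25, linear models on both paths, two-sided Sobel test, 4,000 runs per case. A latent normal mediator is cut into 7 categories with assumed frequencies, then split at 1–2 vs 3 or more.

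| Overall responders (assumed) | 7-point score, a = 0.25 | Binary, a = 0.25 | Binary, a = 0.5 |
|---|---|---|---|
| 10% | 65% | 8% | 23% |
| 20% | 69% | 23% | 74% |
| 30% | 67% | 35% | 90% |
| 40% | 70% | 43% | 96% |
| 50% | 67% | 45% | 97% |
| 60% | 67% | 46% | 96% |

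At a = 0.5 the 7-point score gives over 99% throughout. A repeat run gave 7–47% and 25–98% for the binary form, so the two runs together span 7–47% and 23–98%.

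Using 126 rather than 105 does not rescue the small-path figure. Power of 46% corresponds to z ≈ 1.86; multiplied by √(126/105) = 1.095 this is 2.04, or about 53%.

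**Step 3: information lost by the cut.** Against a continuous normal score, the retained share is φ(z_p)²/[p(1 − p)]: 0.342 at 10% responders, 0.490 at 20%, 0.576 at 30%, 0.637 at 50%. Against the 7-point scale itself (same latent normal model, assumed category frequencies), the loss is 62% at 10% responders, 53% at 15%, 47% at 20%, 38% at 30%, 34% at 40%, 31% at 50–60% and 35% at 70%. The range is therefore roughly 30–60%.

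**Step 4: the primary test (path a alone), small path.** Continuous: z = 0.25/√0.00910 = 2.62, power 75%. Multiplying z by the square root of the retained share gives 2.62 × √0.637 = 2.09 (55%) at 50% responders and 2.62 × √0.342 = 1.53 (33%) at 10%. This is a large-sample approximation and is optimistic at low responder rates.

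**The case against.** The strongest reply has four parts.

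- **The cut is deliberate.** The 1–2 rule is prespecified and matches the responder rule for the CGI-I and CGI-S, and no sentence says in so many words that the binary form enters the mediation model. This is fair, but no other scoring is offered. If the 7-point score is intended, the text should say so.
- **The loss depends on the scenario.** With a moderate path and 30% or more responders, the binary form still has about 90% power or better. This stands. The damage is concentrated in the small path and in low responder rates. The protocol says it has no preliminary data on the effect of RUBIES on self-management, so neither can be set aside.
- **The indirect effect is exploratory.** True, but the same cut weakens the treatment-on-mediator test, which is not exploratory.
- **b, c' and n are partly inferred.** True. The mismatch does not depend on them closely, as the n = 126 scaling shows.

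Two stronger readings are tempting and should not be made. A reader might infer that the plan multiplies a log-odds path by a linear path. No link is stated for the mediator model: the mediation builds on a linear mixed model, and the remark "LMM and Generalized LMM for binary outcomes" concerns the secondary sustainment outcome. With linear models on both paths, the product is in SESBI-R points. The link may also be settled in an analysis plan that is not shown. A reader might also fix the information loss at 40–50%. That fits only about 20–30% responders, and the protocol gives no rate.

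**Conclusion.** The point holds as a mismatch between the stated scoring and the stated power. Every reading found that recovers 67% and 99% uses a continuous standardized mediator. For the binary variable, small-path power stays below 67% at every responder rate examined (about 7–47%), and moderate-path power runs from about 23% to 98%. The information loss is roughly 30–60%.

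These sizes rest on b = 0.5, c' = 0.14–0.25 and a design effect of 1.2 for the reproduction. The binary results also rest on c' = 0.25, a latent normal mediator, assumed category frequencies and responder rates of 10–60%. The direction of the loss does not depend on those choices. This is a worthwhile correction to a mechanism aim and does not touch the Aim 1 or Aim 2 primary comparisons.

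**What to change.** State that the 7-point CGI-SM score is the mediator, both in the primary treatment-on-mediator test and in the exploratory mediation model. Use a linear mixed model, with a cumulative logit model as a check. Keep the 1–2 vs 3 or more split as a descriptive responder rate by arm.

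If the binary form is kept, restate the Aim 3 power for it over a range of assumed responder rates. Should a logit link then be chosen for the mediator, report the indirect effect on the SESBI-R scale rather than as a raw product of coefficients.

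The cost is wording only. The score is already in the assessment schedule, and the Discussion reports no enrolment as of February 2026, so the change can be made before any data exist.
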